## Abstract

**Introduction:**

Resilience is considered of high relevance when developing interventions to cope with stressful situations. Schools are one of the key settings to promote resilience among adolescents. The purpose of this cluster randomized controlled trial is to assess the effectiveness of an intervention in adolescents at risk, aged 12-to-15 years old, to increase resilience and emotional regulation strategies.

**Methods:**

The recruitment period started in January 2022. Schools will be randomly allocated to control and intervention groups by an external researcher using computer-generated random numbers. The minimum sample size was estimated to be 70 participants per group. Primary health care nurses will carry out the intervention during the school period (January to June 2022). Students will follow a specific training consisting of six 55-min sessions, for 6 weeks. Each session will consist of 5 min of mindfulness, followed by 45 min of the corresponding activity: introducing resilience, self-esteem, emotional regulation strategies, social skills, problem-solving, community resources, social and peer support, and 5 min to explain the activity to do at home. Data will be collected at baseline, 6 weeks, and 24 weeks after the intervention. The child youth resilience measure-32 (CYRM-32) scale will be used to assess the effectiveness of the intervention. This study received a grant in June 2021.

**Discussion:**

The intervention is intended to improve mental health through resilience. Different factors related to resilience will be promoted, such as self-esteem, emotional regulation, social and communication skills, problem-solving and peer support, among others. As it has been designed as a cluster-randomized school-based intervention, we will directly ameliorate the participation and engagement of the target population. With the present intervention, we expect to improve coping skills in adolescents by enhancing resilience capacities.

## Introduction

1.

The incidence of mental health disorders in adolescents has become a global health burden (Kieling et al., 2011). The onset of most mental health problems is between 12 to 25 years old, with 20% affecting adolescents (Kessler et al., 2005; Wei et al., 2013).

During the COVID-19 pandemic, social inequalities widened and mental health problems in adolescents increased (Gracia et al., 2021; Hermosillo-de-la-Torre et al., 2021). Studies showed that during the pandemic, depression, anxiety symptoms, stress (Varma et al., 2021), and suicidal behavior (Gracia et al., 2021) increased among adolescents. Furthermore, several other risk factors affect the mental health of adolescents. Risk factors are those conditions related to the environment that increase the possibility of suffering poor adjustment or have negative effects on physical, mental, social health, or academic achievement (Braverman, 1999). The main risk factors identified in the literature are poverty or low socioeconomic level, maltreatment and sexual abuse, low-quality family environment, negative life events, and parents with mental disorders, among others (Llistosella et al., 2022). However, not all adolescents exposed to risk factors develop psychological distress. It is at this point that the phenomenon of resilience may appear.

Resilience is a phenomenon observed in adverse contexts, where risk factors can negatively impact psychological development (Wright et al., 2013). It is a dynamic and complex process (Masten, 2001) where many protective factors are involved. Protective factors can grow and develop over time, changing an individual capacity to face adversity and risk factors (Liebenberg, 2020).

Some models of resilience have been developed based on Bronfenbrenner (1981) and his theory of child development within a system of interactions between himself or herself and his or her immediate environment (family, social-wide: community and culture). These models organize in different domains diverse proximal and distal factors related to resilience that come from various environments (e.g., home, school, individual, etc.). They also describe the interactions between factors, domains, and individuals (Ungar, 2006; Llistosella et al., 2022).

For instance, Ungar’s resilience model, includes a new constructivist perspective, because they considered not only the internal aspects of the individuals and their interaction within different environment levels, but also, their cultural diversity which influenced individuals’ behaviors, beliefs, and relationships (Ungar, 2006; Ungar and Liebenberg, 2011). Most recently, we developed the Individual & Environmental Resilience Model (IERM) for adolescents and young adults (Llistosella et al., 2022). This model includes the main protective factors involved in resilience: relationships and social support, school engagement, presence of a positive mentor, family support, parental quality (e.g., housing, food, no violence), rules and routines, physical activity, coping, expressive skills, confidence, optimism, self-esteem, social skills and self-regulation (Llistosella et al., 2022). The IERM describes two major dimensions of resilience: (a) *Environmental*: including family, school, peers, cultural and community domains; and (b) *Individual skills:* including biological, behavior, communications, cognitive and emotional domains.

Resilience is related to positive mental health and it is also defined as good mental health and psychosocial functioning despite exposure to risk or adversity (Collishaw et al., 2016). Among children and adolescents, resilience encourages positive development, strengthens positive relationships with family and peers, increases success at work and school, improves coping mechanisms to adapt to adverse situations, and decreases the predisposition for anxiety, depression, and stress (Connor and Zhang, 2006; Masten et al., 2008). One specific resilience factor, the emotion regulation strategy (cognitive reappraisal and expressive suppression) included in self-regulation skill, has a positive impact on well-being, relationships, and social and psychological outcomes (Azpiazu Izaguirre et al., 2021; Yıldırım and Arslan, 2022).

Given the complexity of resilience, its promotion must be done with an appropriate intervention approach. Three different ways have been proposed: *Risk Reduction*, which focuses on reducing exposure to adversity; *Attentive to Assets*, which intends to increase the resources and their quality; and *Process-oriented*, which improves the life of the person at risk, instead of limiting susceptibility to risk or rising the number of resources (Masten et al., 2008).

For more than a decade, schools have been considered one of the key points to promote resilience and mental health (Greenberg, 2006). Several promoting-resilience training programs have been created and carried out in different contexts and populations, using different configurations, timings, and settings (Chmitorz et al., 2018), and have been proven effective (Suranata et al., 2020; Volanen et al., 2020; Zhang et al., 2021). Resilience interventions, based on cognitive-behavioral therapy (CBT; Dray et al., 2017) or, CBT with mindfulness techniques (Joyce et al., 2018), reduce depressive and anxiety symptoms, and positively influence individual resilience. Multicomponent interventions, for example, based on counseling or expert sports program, have shown effectiveness in increasing psychological resilience and reducing emotional disorders in adolescents with anxiety symptoms (Zhang et al., 2021). However, some other multicomponent interventions, have shown effectiveness in increasing only one of the resilience domains, but not as a whole (Kelley et al., 2021; Tripa et al., 2021). Therefore, there is a need to increase evidence on effective resilience interventions and especially those promoting mental well-being (Goldberg et al., 2019; European Commission, 2020).

Furthermore, most of the interventions previously done to promote resilience and mental health among adolescents have been conducted primarily by professionals other than nurses (Sugiyama et al., 2020; Kelley et al., 2021; Tripa et al., 2021). Primary healthcare is the first level of contact in the health system for individuals, families, and the community. The role of primary and community care nurses is a key piece for health promotion and prevention (Kemppainen et al., 2013). Nurses are strategically positioned to educate adolescents as active agents for their own health, to minimize risk behaviors, and promote positive lifestyle practices (Ahern et al., 2008). Adolescents should be at the centre of nursing practice, as well as their social and family environments. Indeed, nurses act as protective and facilitating actors for successful self-development and community skills for adolescents. It is fundamental to get them involved in the development, implementation, and assessment of interventions fostering resilience.

Based on the presented evidence and considering that about 70 to 80% of the population does not receive adequate care for mental health issues (Thornicroft, 2007), the promotion of resilience among adolescents could be appropriate for facing adversity in a stressful context such as the COVID-19 pandemic. Based on the IERM, the present protocol aims at describing a school-based resilience intervention to foster protective factors (individual, cultural, relational and community) in adolescents at risk, highlighting the role of the primary care nursing team as the main actor and driver of the intervention.

## Study objectives and hypotheses

2.

### Objectives

2.1.

Evaluate the effectiveness of an intervention on resilience capacities in adolescents at risk aged 12-to-15Increase the emotional regulation strategies of adolescents at risk aged 12-to-15.Evaluate the association between resilience intervention and depressive symptoms in adolescents at risk aged 12-to-15 years.

### Research hypothesis

2.2.

We hypothesize that adolescents at risk between 12-to-15 years old, who receive a resilience school-based intervention, will increase their resilience capacities and emotional regulation strategies compared to the control group. Resilience will be associated with a decrease in depression symptoms in the adolescents who received the intervention compared to the control group.

## Methods and analysis

3.

### Design

3.1.

This study is a cluster-randomized controlled trial with parallel arms. Clusters will be school classrooms (grades 6, 7), subjects aged 12-to-15 years.

### Participants

3.2.

#### Inclusion criteria

3.2.1.

Adolescents (girls and boys) aged 12-to-15 in a context of risk (risk of social exclusion or COVID-19 pandemic)Adolescents/parents who consent to participate in the study.

#### Exclusion criteria

3.2.2.

Adolescents (girls and boys) aged 12-to-15 who do not want to participate in the activities of the intervention.

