### Study setting and data collection

3.3.

Recruitment will begin after the start of the school year and the intervention will be carried out by the primary health care nurses throughout the school period (January/June 2022). Public or concerted (private schools which receive public funds or subsidies) schools in neighborhoods at risk of social exclusion from Terrassa, Manresa and Barcelona (Spain) will be invited to participate.

Before starting the intervention:

An interdisciplinary committee of nine experts reviewed the intervention program and protocol in order to validate the contents and to ensure the relevance and appropriateness of the activities included in the intervention. The committee includes two psychologists, one social worker, and six primary health care and school nurses. Additionally, two adolescents at risk were included in the committee to develop the intervention and ensure the engagement of participants.

These nurses will be trained during two training sessions about resilience and activities included in the intervention.

Researchers will contact the selected schools and will discuss the study with school directors and teachers, answering the questions and reviewing the consent forms. The representatives of the schools will sign the participation agreement.An online informative session for parents/carers will be held, where doubts will be solved.A letter with the informed consent and relevant information from the study will send to parents/carers by schools.Once the informed consent is returned from parents/carers, adolescents will receive a session with age-appropriate information about the study in their classroom conducted by their teachers and research team.Assent from the adolescents will be obtained.For adolescents who do not assent, each school will prepare another activity depending on each school. For example, readings sessions, time for studying or homework

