#### Control group

3.4.2.

The control group will complete different activities depending on each school. As it has been stated: reading sessions, time for studying or homework, etc. They will fill in the same research questionnaires as the intervention group and during the same period (January to December 2022).

Schools in the control group will be all waitlisted to receive the intervention during the following academic year should if it proves to be effective.

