### Blinding

3.8.

Given the difficulty in masking any condition, participant groups and personnel (research team) will not be blinded.

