### Data analysis

3.9.

An intention-to-treat analysis will be performed. A descriptive analysis of the variables will be carried out, with frequency and percentage for the qualitative variables; mean and standard deviation for the quantitative normal distributed variables and median and quartiles for the quantitative not-normal distributed variables. The values from the scores for the intervention and the control group will be compared with the *t*-student test if the score is normally distributed, with the Mann–Whitney test if the score is not-normally distributed and if the score has a cut-off, it will be compared with chi-square test. The effect size will be calculated as the difference of means and with ratio of proportions (with its corresponding confidence intervals).

A linear regression and a logistic regression will be considered including other variables that can affect the response. Also, we will stratify the results for other factors like gender, age and others than will be considered. To check normality, the Kolmogorov–Smirnov test and the Shapiro–Wilk test will be used. All the confidence intervals will be performed with a 95% confidence level. All the analysis will be performed with the software R version 4.2.2.

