### Consent process

5.2.

The study will be carried out in compliance with current legislation, by following the Biomedical Research Law 14/2007. The confidentiality of participants’ data will be guaranteed, in compliance with Organic Law 3/2018, of 5 December, on the Protection of Personal Data and the guarantee of digital rights and the General Data Protection Regulation (EU) 679/2016.

First, secondary school directors who will participate in this research will sign an agreement and attachment to the study. Second, an online session with parents/carers of the selected schools will be held to explain the study and the intervention. Third, before being registered for the study, the schools will send a letter with all relevant information about the study and the written informed consent form (in both languages, Catalan and Spanish, to parents/carers). Parents/carers will return the informed consent form (ICF) signed and they will keep a copy. ICF from participants will be obtained after an informative session (with age-appropriate information) in the classroom conducted by their teachers and the research team. If the parents/carers give consent, but the adolescents do not want to participate in the study, the decision of the participants will prevail and will be respected. For adolescents with difficulty with written information, visual information sheets will be provided. Each participant will be identified by a serial number and the initials of the first and last name. Only the principal investigator and collaborating researchers will have access to the collected data.

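### The only exclusion criterion is tied to the intervention's activities, so as worded it may select students differently in the two arms

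*Protocol article*

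**What the plan says.** All references are to the protocol article.

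- **Inclusion (3.2.1):** consent is defined by reference to the study: "Adolescents/parents who consent to participate in the study".
- **Exclusion (3.2.2):** the single criterion is defined by reference to the programme. It covers adolescents aged 12 to 15 "who do not want to participate in the activities of the intervention".
- **Consent process (5.2):** refusal is again refusal of the study. If parents agree but "the adolescents do not want to participate in the study, the decision of the participants will prevail and will be respected".
- **Study setting (3.3):** consent and assent are listed under "Before starting the intervention", with no distinction by arm. "For adolescents who do not assent, each school will prepare another activity depending on each school", with reading, study time or homework as examples.
- **Control group (3.4.2):** "The control group will complete different activities depending on each school", with the same examples. Control schools are waitlisted for the following academic year, on condition that the programme proves effective.
- **Randomisation and blinding (3.7, 3.8):** schools are allocated first, and "participant groups and personnel (research team) will not be blinded".
- **Analysis (3.9):** "An intention-to-treat analysis will be performed". The analysed population is not described further.

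**The concern.** Two different refusals are in play: refusing the study (sections 3.2.1 and 5.2) and refusing the programme's activities (section 3.2.2). If they meant the same thing, the exclusion would add nothing to the inclusion criterion. Read literally, it adds one kind of student: someone who would complete the questionnaires but does not want the sessions. In an intervention school that student meets the exclusion. In a control school there are no sessions to decline during the trial, so the counterpart is likely to stay in.

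The programme is group work on emotions, with role-play. Students who do not want it could plausibly differ in resilience or mood, which are the trial's outcomes. If they leave one arm only, the arms differ in composition before the programme has any effect, and a larger sample does not remove that difference.

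**Working it through.** **1. The plan's own figure.** Inputs from section 3.6: difference 10 points, SD 20, alpha 5% (taken as two-sided), power 80%, loss 10%.

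n = 2 × (1.960 + 0.842)² × 20² / 10² = 62.8, rounded up to 63 per group; 63 / 0.90 = 70.

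The stated 70 per group reproduces. (A one-sided alpha gives 50, or 56 after loss, and does not.) This point does not change that figure; it supplies the 10-point target and the SD used as yardsticks below.

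**2. What the text fixes and leaves open.**

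| Question | Protocol article |
|---|---|
| Who runs the activities during the trial? | Intervention schools only (3.4.1, 3.4.2) |
| Is the exclusion limited to one arm? | Not stated (3.2.2) |
| How is it applied in control schools? | Not stated |
| Is assent taken before the intervention? | Yes (3.3) |
| Is assent taken before allocation is disclosed? | Not stated (3.3, 3.7) |
| Are enrolled students who stop attending removed from the analysis? | Not stated; intention-to-treat is announced (3.9) |

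**3. Size, under assumptions.** Let p be the share of students unwilling to do the activities (the same in both arms), and d the number of points by which their mean lies below that of willing students. Suppose the programme has no effect.

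- Intervention arm with unwilling students removed: mean = m, the mean of the willing.
- Control arm with nobody removed: mean = m − p × d.
- Spurious difference = p × d.

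The document gives neither p nor d. Taking d = 10 points (0.5 SD):

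- p = 5%: 0.05 × 10 = 0.5 points, 5% of the target.
- p = 15%: 0.15 × 10 = 1.5 points, 15% of the target.
- d = 0: no bias at any p.
- d = −10 (unwilling students score higher): −0.5 to −1.5 points, against the intervention.

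If a fraction f of the unwilling is also excluded in control schools, the difference becomes d × p(1 − f) / (1 − p × f). With p = 15%, d = 10 and f = 0.5 this is 10 × 0.075 / 0.925 = 0.81 points; with f = 1 it is zero.

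**4. Effect on the test.** Normal approximation, SD 20, clustering ignored, SE = 20 × √(2/n). Under no programme effect, the chance of a nominally significant result at 5% is Φ(b/SE − 1.96) + Φ(−b/SE − 1.96), where b is the bias.

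| Bias b | n = 63 per arm (SE 3.56) | n = 337 per arm (SE 1.54) |
|---|---|---|
| 0 | 5.0% | 5.0% |
| 0.5 | 5.2% | 6.2% |
| 1.5 | 7.1% | 16.4% |

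The 337 is the 674 recruited students (section 4) split equally, which is an assumption. The same bias matters more in the larger sample because the standard error shrinks and the bias does not.

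**The case against.** The strongest reply is that section 3.2.2 is loose shorthand for non-assent. It carries no arm qualifier, sections 3.3 and 5.2 describe consent and assent without distinguishing arms, and willingness could be asked in every school, including waitlisted ones, before allocation is known. Exclusion at enrolment on those terms would be compatible with intention-to-treat. That non-assenters and controls do similar things shows only what schools offer students who are not in a session; it does not date the disclosure of allocation. The absence of blinding does not date it either.

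Much of this stands, and it rules out three stronger readings that a reader might infer:

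- *The criterion can act only in the intervention arm.* The text does not say so.
- *It contradicts intention-to-treat.* Nowhere does the article say that an enrolled student who misses or leaves sessions is dropped.
- *The planned tests discard students without follow-up scores, so intention-to-treat is not delivered.* The article is silent on missing data, a statistical analysis plan that is not shown may cover it, and the 10% in section 3.6 is an allowance in the sample size, not an analysis rule.

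What the reply does not remove is the wording. The exclusion names the programme's activities where the neighbouring sections name the study, and no stated safeguard ensures that it acts alike in both arms.

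**Conclusion.** The point holds as a risk of differential selection, not as a demonstrated bias. Followed as written, in an unblinded trial that allocates schools, the criterion can exclude students willing to be measured in one arm and keep their counterparts in the other. Bias requires both unequal application and a different outcome among unwilling students. The document establishes neither, so size and direction stay unknown. The 0.5-1.5 point range rests wholly on the assumed 5-15% refusal, the assumed 10-point deficit, and no matching exclusion in control schools. Even then it is modest beside the 10-point target, though not negligible at the recruited sample size. Intention-to-treat would be undermined only if the criterion were applied to students who had consented to the study and then declined sessions. It should be corrected: the change is cheap, and section 4 shows that analysis was still in progress.

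**What to change.** 1. Replace the exclusion with absence of parental consent or student assent to the study, meaning its questionnaires, in identical words for both arms.
2. Define the intention-to-treat set as every consented student, analysed in the arm of their school whatever their session attendance.
3. State whether assent in each school preceded disclosure of that school's allocation.
4. Report refusal counts by arm and school within the cluster CONSORT reporting already promised in section 3.3, and give baseline scores of consented students who declined sessions. Students who refused the questionnaires will have no scores, so only their numbers can be given.

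Recruitment is complete, so rewording cannot change who was enrolled. Items 2 to 4 apply directly to the analysis set and the report; item 1 serves as the rule for keeping any consented student who might otherwise be removed for declining sessions.

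The cost is one eligibility sentence, a definition of the analysis set and some reporting. Non-attenders will dilute the estimate somewhat, which is what an intention-to-treat comparison accepts.
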